### Design of the study

This study is a community, multicentre, parallel clinical trial, randomised by clusters, that compares usual care and an education strategy performed by primary healthcare professionals. The intervention will be carried out with mother-infant pairs in ten PHCCs in the Community of Madrid (Spain).

The randomization units will be the PHCCs (clusters). The units of analysis are the mother-infant pairs attended to by the PHCCs. This design by clusters minimises possible contamination effects between centres.

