### Sample size

To calculate the sample size, we believe that the educational group intervention can increase the proportion of mother/infant pairs that use EBF at six months by 15%. Assuming that 24% of mothers use EBF at six months (National Health Survey (2006). National Statistics Institute http://www.ine.es), a type I error of 5% and a strength of 80%, we need a sample of 150 mother/infant pairs in each group. As this is a randomized design with conglomerates (each conglomerate is a health centre), the sample size needs to be increased taking into account the effect of the design (ED = 1+ (ñ-1)*CCI, where ñ is the average size of each cluster and CCI is the intra-class coefficient of correlation).

Considering a CCI of 0.01 and an average size of 30 pairs per centre, the effect of the design is 1.29. Taking this data into account, the sample size increases to 194 pairs in each group. If we then take into account the loss rate of 10%, the total size surpasses 432 pairs (216 for each branch).

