### Randomisation

The randomisation unit will be the healthcare centres.

An independent statistician will carry out the randomised allocation to form groups of the same size from a list of the participating healthcare centres.

Posteriorly, within each unit, the mother-infant pairs will be selected by consecutive sampling, until the number is reached to form the cluster. Figure 1 describes how the pairs are recruited. During the consultations, the mothers will be informed about the study and asked if they would like to participate. All mothers that would like to have to sign a consent form and it will be confirmed that they meet all inclusion/exclusion criteria.

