### Statistical analysis

The database will be filtered before the statistical analysis is performed to improve the quality of the data collected. The use of the design by conglomerates will be taken into account in all phases of the analysis, especially when calculating the confidence intervals of the estimations and in the hypothesis tests. The following will be carried out:

1. Descriptive analysis of the demographic and baseline characteristics of the subjects of both groups. The quantitative variables will be described by their measurements of central, mean or median tendencies, in the case of asymmetrical distributions, and their measurements of dispersion, typical deviation or interquartile amplitude, respectively. The qualitative variables will be described by their proportion and confidence interval.

2. Initial comparability study of the two groups regarding their baseline characteristics, response variables and prognostic factors. The Student t test or the Mann-Whitney test will be used if the normality hypothesis is rejected for the data. If the study variables are qualitative, the Pearson’s Chi-squared test or Fisher’s exact test will be used, when applicable. In the case of inequality, the possible confounding factors will be defined by which the final analysis of the principal variable of effectiveness will be adjusted.

3. Principal analysis of effectiveness. The effect of the PROLACT intervention in the principal response variable: a comparison will be made of the proportion of mother/child pairs using EBF at six months in both groups, using Fisher’s exact test, while also estimating the confidence interval for the difference. If the confounding factors were distributed in an unequal manner in each group, a model will be constructed of explicative logistical regression where the dependent variable will be EBF at six months and the independent variable will be “treatment” group adjusted for the possible confounding factors. The analysis of effectiveness will be done by intention-to-treat.

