4. Analysis of secondary effectiveness. To evaluate the effect of the educational group intervention on the duration of the different types of breast-feeding, an analysis of survival will be done, making the comparison between the two groups using the log-rank test. The control of the possible confounding variable will be done with the construction of different Cox regression models. The proportion of women that attend at least 85% of the planned sessions will be calculated to study the degree of adherence. The women’s satisfaction with the educational group intervention will be measured with a Likert-type scale.

All *p*-values below 0.05 will be considered as statistically significant for all cases.

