- As it is a non-pharmacological intervention, there may be differences in the manner in which the different professionals carry it out. Training sessions on the educational group intervention will be carried out to minimize said differences [37].

-The observations of the result variables of the individuals from the same cluster tend to be positively correlated with those of other members of the same cluster and thus we cannot assume statistical independence [38].

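### The protocol promises cluster-adjusted tests but names Fisher's exact test on individual pairs as the primary test; in standard form that test cannot keep the promise

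*Protocol article*

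**What the plan says.** All references are to the protocol article.

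- **Design of the study** sets the levels of randomisation and analysis: "The randomization units will be the PHCCs (clusters). The units of analysis are the mother-infant pairs attended to by the PHCCs". The setting is "mother-infant pairs in ten PHCCs in the Community of Madrid (Spain".
- **Randomisation** makes the arms equal in number of centres, so five against five: "An independent statistician will carry out the randomised allocation to form groups of the same size".
- **Statistical analysis, opening paragraph**: "The use of the design by conglomerates will be taken into account in all phases of the analysis". The same sentence singles out confidence intervals and hypothesis tests.
- **Statistical analysis, item 3** (primary): "a comparison will be made of the proportion of mother/child pairs using EBF at six months in both groups, using Fisher’s exact test". A confidence interval for the difference is to be given, with no method named. Logistic regression follows only if confounders turn out to be unequally distributed, and no centre term is mentioned.
- **Statistical analysis, item 4** (duration): "making the comparison between the two groups using the log-rank test". Cox models follow, again with no mention of centre.
- **Discussion, limitations**: outcomes within a centre are described as positively correlated, "thus we cannot assume statistical independence".

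**The concern.** Fisher's exact test is the only primary test that will be run whatever the data show. It takes its p-value from a 2×2 table of independent pairs, and a design effect cannot be entered into it. An analyst who follows item 3 literally breaks the opening paragraph. One who follows the opening paragraph must replace the test in item 3, and the article does not say with what.

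At stake is the 5% error rate of the primary comparison. If pairs are analysed as independent, ordinary variation between centres counts as evidence for the intervention. The Discussion intends to extend the programme to all healthcare centres. An open choice also matters in practice: a pair-level test and a centre-level test can disagree on the same data, so the method should be settled before the data are seen.

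**Working it through.** **1. The plan's own sample size (Sample size section).** The inputs are a control rate of 24% ("Assuming that 24% of mothers use EBF at six months"), a rise of 15 points to 39%, alpha 5% taken as two-sided, and power 80%.

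n per arm = [1.96·√(2·0.315·0.685) + 0.8416·√(0.24·0.76 + 0.39·0.61)]² / 0.15² = 149.4, rounded up to 150.

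Design effect = 1 + (30 − 1)·0.01 = 1.29. Then 150 × 1.29 = 193.5, rounded up to 194, and 194/0.9 = 215.6, rounded up to 216 per arm, 432 in total. All the stated figures reproduce. The design therefore allows for clustering; the question is whether the named test does.

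**2. Cluster size for the check.** With five centres per arm, the 194 analysed pairs give 194/5 = 38.8 per centre. The planning average of 30 is smaller, so both are shown.

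**3. Normal approximation.** If clustering is ignored, the true level of a nominal 5% test is 2·[1 − Φ(1.96/√DE)], where DE is the design effect. At ICC 0.01:

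| Pairs per centre | DE | True SE / naive SE | True level |
|---|---|---|---|
| 30 | 1.29 | 1.14 | 8.4% |
| 38.8 | 1.38 | 1.17 | 9.5% |
| 43.2 (432/10, no losses) | 1.42 | 1.19 | 10.0% |

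**4. Simulation of Fisher's test.** Fisher's test is conservative, so the approximation overstates its error. A beta-binomial simulation used 5 v 5 centres with 39 pairs each. There were 40,000 runs with 24% in both arms, and 20,000 runs with 24% v 39% for power. Only ICC 0.01 comes from the protocol; the other values are assumptions.

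| ICC | Fisher, type I error | Centre t-test (8 df), type I error | Unadjusted 95% Wald interval, coverage | Centre t-test, power |
|---|---|---|---|---|
| 0 | 3.9% | 5.2% | 94.8% | 80% |
| **0.01** | **7.9%** | **5.2%** | **90.0%** | **67%** |
| 0.02 | 11.9% | 4.9% | 85.8% | 57% |
| 0.03 | 15.8% | 5.0% | 81.6% | 49% |
| 0.05 | 22.5% | 4.9% | 74.8% | 38% |

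For scale, the standard deviation of true centre rates is √(ICC·0.24·0.76). That is 4.3 percentage points at ICC 0.01 and 9.5 at 0.05.

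**5. Analytic check of the centre-level power.** At ICC 0.01, SE = √[(0.1824 + 0.2379)·1.378/194] = 0.0546. The non-centrality is 0.15/0.0546 = 2.75, and with 8 df (critical value 2.306) power is 67%. In the same setting Fisher's test rejects in 83% of runs, but at a level that is not 5%.

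**The case against.** The strongest defence is that the opening sentence governs everything after it. On that reading the article only names families of methods, and the full protocol or analysis plan would supply the clustered versions. The trial plainly did not overlook clustering: the design, sample size and Discussion all recognise it.

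For most of the section this defence stands. A reader might infer that the trial's intervals will be too narrow, or that the log-rank, logistic and Cox analyses will ignore centres. The article does not support either as fact. No interval method is named, and the undertaking expressly covers intervals. Logistic and Cox models have random-effect or frailty versions, and a log-rank statistic can be referred to permutations of centres. Leaving those details to another document is normal for an article.

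The defence fails for Fisher's exact test. There the article names a specific test, and its standard form has no clustered version for an analysis plan to fill in. Such a plan could keep the promise only by departing from the named test.

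The size should not be overstated either. At the only ICC the protocol gives, the excess error is modest, and the larger figures depend on ICCs that it does not state.

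**Conclusion.** The Statistical analysis section contradicts itself on the primary test. It commits to handling clustering in hypothesis tests, then fixes a test that in standard form assumes independent pairs, an assumption that the Discussion rejects. The contradiction rests on the text alone.

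Its consequence is conditional on the test being run as named. With five centres per arm and about 39 analysed pairs each, the true type I error is about 7 to 8% instead of 5% at ICC 0.01, and 12 to 22% over the assumed range 0.02 to 0.05. The coverage of about 90% at ICC 0.01 applies only if an unadjusted Wald interval were chosen. The calculations assume equal centre sizes and beta-binomial variation between centres.

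This should be corrected before analysis because it concerns the only unconditional test of the primary outcome.

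**What to change.** **Primary analysis.** Replace Fisher's exact test by one named method that carries the centre effect and suits ten clusters. Two suitable choices are:

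- a t-test and confidence interval on the ten centre-specific EBF proportions, with 8 df;
- a mixed logistic model with a random centre effect and a small-sample correction.

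Name the interval method at the same time.

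**Other analyses.** State how each keeps the promise: a random centre effect in the logistic model, a centre frailty in the Cox models, and permutation of centres for the log-rank test. Unrestricted 5 v 5 allocation gives 10!/(5!·5!) = 252 arrangements. Centre should not be entered as a fixed covariate: each centre belongs to one arm, so its effect would be collinear with treatment.

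**Cost.** Only wording changes; no data collection is affected. Compared with a normal interval that ignores centres, the centre-level interval at ICC 0.01 is about √1.378 × 2.306/1.96 = 1.38 times as wide. Of this, a factor of 1.17 is the design effect and 1.18 the use of t with 8 df. Power for 24% v 39% with the centre-level t-test is about 67 to 68% at ICC 0.01, so the stated 80% should be restated for the analysis chosen.

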## Discussion

Revisions of other studies show us that education and supportive interventions, both for breast-feeding women as well as for healthcare professionals, can increase the proportion of women that use EBF [29, 30, 35, 36].

As concluded in the Cochrane review by Britton C, more evidence is needed on the effectiveness of group interventions. Generalization should be preceded by the development of clinical trials that measure relevant clinical results in patients, that surpass the limitations of the studies designed to today’s date and that are conducted in the setting in which they will be implemented [29].

The majority of the interventions have been conducted in hospital settings (or maternity wards) or in countries that present socio-cultural differences [32] from Spain. Therefore, studies are needed in the contact of Primary Healthcare, with the fundamental purpose being the promotion of health lifestyle habits and where mothers-infants receive the greater part of healthcare.

Our proposal as a research group in the setting of the promotion of BF in primary healthcare is the PROLACT study, with which we aim to measure the effectiveness of educational group intervention of the General Directorate of Primary Healthcare, to later generalize its implementation in all Healthcare Centres.

The design selected is the most adequate given the characteristics of the intervention. Although a sufficient number of clusters will be selected to equilibrate the randomisation of potentially confounding factors, the following limitations must be taken into account:

- The participation of professionals in the study is voluntary and bias may be produced in the selection of the sample.

- There are healthcare centres professionals that are highly motivated regarding breast-feeding in the Community of Madrid that, during randomisation, may be assigned to the control group. Given that an intention-to-treat analysis will be performed, the mothers attended to in these centres will be analysed in the study branch in which they were assigned by randomisation, that is, the control group, regardless of the intervention that they receive in practice. This fact could generate a tendency to underestimate the effect of the intervention being studied.

- The lack of blinding in a study in which the majority of the variables are self-referred by the mothers.

- As it is a non-pharmacological intervention, there may be differences in the manner in which the different professionals carry it out. Training sessions on the educational group intervention will be carried out to minimize said differences [37].

-The observations of the result variables of the individuals from the same cluster tend to be positively correlated with those of other members of the same cluster and thus we cannot assume statistical independence [38].

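### Ten centres, five per arm with equal size as the only stated restriction, cannot be relied on to balance centre-level confounders as the Discussion claims

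*Protocol article*

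**What the plan says.** The Design of the study section makes the health centre the unit of randomisation and sets the number of centres at ten. The Randomisation section gives the method in one sentence: "An independent statistician will carry out the randomised allocation to form groups of the same size from a list of the participating healthcare centres". It mentions no stratification, matching or constraint on centre characteristics.

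The Discussion then opens its list of limitations with "Although a sufficient number of clusters will be selected to equilibrate the randomisation of potentially confounding factors". One of those limitations is that professionals highly motivated about breastfeeding "may be assigned to the control group". Their mothers would still be analysed as controls under intention-to-treat, whatever care they received, and the protocol concludes: "This fact could generate a tendency to underestimate the effect of the intervention being studied".

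The stated remedy comes after allocation. The Statistical analysis section compares the groups at baseline with t, Mann-Whitney, chi-squared or Fisher tests. It then provides for adjustment for whatever is found unequal, in a sentence that begins "In the case of inequality, the possible confounding factors will be defined by which the final analysis of the principal variable of effectiveness will be". The Variables section lists age, sex and breastfeeding training received for the professionals. It lists no measure of motivation.

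**The concern.** The protocol offers the number of clusters as the reason why confounders will be balanced. Balance by numbers depends on how many units are randomised, and here that is ten, however many mothers each centre recruits. The same paragraph goes on to describe centres that differ in a way likely to affect the outcome.

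A centre-level imbalance is carried by every mother in the centre. With ten clusters and two arms, only 8 cluster degrees of freedom remain, so there is little room to correct the imbalance afterwards. A reader who accepts the sufficiency claim would think this source of error had been dealt with by design.

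**Working it through.** **Inputs from the protocol.** Ten centres (Design of the study); equal groups, hence five per arm (Randomisation); EBF of 24% at six months, a 15-point increase, ICC 0.01 and 30 pairs per centre (Sample size).

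**The protocol's own figure.** Two proportions, 24% v 39%, two-sided 5%, 80% power, no continuity correction: 150 per arm. Design effect 1 + (30 − 1) × 0.01 = 1.29; 150 × 1.29 = 193.5, rounded up to 194; 194 / 0.90 = 215.6, rounded up to 216. This reproduces the stated 432 in total, so the point does not rest on an arithmetic error there.

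**Number of allocations.** C(10,5) = 252.

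**Balance on a continuous centre factor.** The difference between two means of five centres has SD √(1/5 + 1/5) = √0.4 = 0.632 centre SDs. By normal approximation:
- P(|difference| > 0.5 SD): 0.5 / 0.632 = 0.79, giving 43%.
- P(|difference| > 1 SD): 1 / 0.632 = 1.58, giving 11%.
- For comparison, P(> 0.5 SD) would be 26% with ten centres per arm and 11% with twenty.

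**Balance on motivated centres.** The protocol does not say how many of the ten are highly motivated, so their number k is an assumption, shown as a range. The probability that all k fall in the same arm is 2 × C(10 − k, 5 − k) / 252.

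| k | Calculation | All in one arm |
|---|---|---|
| 2 | 2 × 56 / 252 | 44% |
| 3 | 2 × 21 / 252 | 17% |
| 4 | 2 × 6 / 252 | 5% |
| 5 | 2 × 1 / 252 | 0.8% |

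By symmetry, half of each probability belongs to the control arm and half to the intervention arm.

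**Translation to the outcome.** The between-centre SD of the EBF proportion is √(ICC × 0.24 × 0.76). Multiplying by 0.632 gives the SD of the arm difference due to centres.
- ICC 0.01 (protocol): 4.3 points × 0.632 = 2.7 points.
- ICC 0.05 (assumption): 9.5 points × 0.632 = 6.0 points.

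These are upper limits for any one factor, because they treat it as explaining all the variation between centres. The planned effect is 15 points.

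**The case against.** Several arguments on the other side stand and limit the point.

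- Equal-size cluster randomisation is valid. Chance imbalance between centres is part of the between-cluster variance. The design effect includes it, and the Statistical analysis section undertakes to allow for clustering in intervals and tests. A reader might infer that the trial is biased by design; the documents do not support that.
- A reader might also take the sentence on underestimation as a one-sided account of baseline imbalance. In context it concerns control mothers who receive care similar to the intervention and are still analysed as controls. That dilution does pull towards no effect, so the sentence is sound for what it describes. The protocol also does not say that all motivated centres would be controls, only that such centres could be.
- Planned adjustment is not confined to the mothers' characteristics. Staff breastfeeding training is among the listed prognostic variables and could enter the logistic model.
- The article may condense the randomisation procedure. Missing stratification detail alone would be a weak finding.
- At the protocol's ICC the shift is small beside the 15-point target.

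None of this supports the sufficiency claim, which the article makes positively and which ten centres do not bear out. The adjustment does not fill the gap either: it depends on baseline tests, has no motivation variable to use, and has few cluster degrees of freedom to spend.

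**Conclusion.** The point holds in a limited form. Ten centres under equal-size allocation alone cannot be relied on to balance centre-level confounders, and the statement that the number of clusters is sufficient for this is unsupported.

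The consequence is a moderate and partly avoidable loss of precision: a chance shift with an SD of up to about 2.7 points at the protocol's ICC of 0.01, or about 6 points if the ICC were 0.05. The shift can go either way. The results rest on five centres per arm, a normal approximation for the centre factor, and the assumption that no further restriction on allocation exists beyond the one stated. The figures for motivated centres also depend on their assumed number. The change is worth making because it costs little, not because the design is invalid.

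**What to change.** 1. **Allocation.** Replace simple equal-size allocation with constrained randomisation. List the 252 allocations, keep those balanced on two or three centre factors known beforehand (for example staff breastfeeding training or accreditation, socio-economic level of the area, centre size), and draw one at random.
2. **Analysis.** Include the same factors in a cluster-level analysis, or in a permutation analysis over the retained allocations, regardless of baseline p-values.
3. **Text.** Delete the claim that the number of clusters is sufficient for balance. Keep the statement on dilution under intention-to-treat. Add that chance imbalance of motivated centres can shift the estimate in either direction.

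**Cost.** A few hours of the independent statistician's time, and basic centre data before allocation, which Table 1 places two months before the first visit. The retained set must stay large enough, about 100 or more of the 252: with 100 allocations the smallest two-sided permutation p-value is 2/100 = 0.02, against 2/252 = 0.008 for the full set. If the centres have already been allocated, items 2 and 3 still apply, with the factors fixed before outcome data are seen and any permutation analysis run over all 252 allocations.
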